##### Initial conservative management (group B)

Patients randomized to group B will be conservatively managed on a clinical medium neurocare ward or intensive care unit using a TBI treatment protocol based on the BTF. On the ICU, the diagnostic and therapeutic options include ICP monitoring with medical management of intracranial hypertension (i.e., hyperosmolar therapies, hyperventilation) and CPP guided treatment. On the ward, monitoring increased ICP by clinical observation can include waking the patient on predefined time points (every hour during the first 24 to 48 h). Patients initially randomized to group B, who experience significant neurological deterioration, defined as a decrease of GCS score of ≥3 points, will receive delayed secondary hematoma evacuation after a repeated CT scan as deemed necessary by the treating neurosurgeon and will stay within group B as this is an ITT design. Similarly, group B patients who undergo secondary burr hole drainage within 6 months after initial trauma will be analyzed as a subgroup within group B. Alternatively, on the discretion of the treatment team (neurosurgeon, ICU doctor, and neurologist) and communication with the family it can be decided that “comfortable end-of-life care” is more appropriate than surgery. The principle that “the interest of the patient always prevails over those of science and society” will apply in this study.

##### Observational cohort (group C)

An observational cohort group (C) containing all elderly patients with a traumatic ASDH presenting to one of the participating centers during the inclusion period, including those who meet the exclusion criteria for randomization or die before randomization, will be registered parallel to the randomized groups in the form of a screening log.

### Criteria for discontinuing or modifying allocated interventions {11b}

Subjects can leave the study at any time for any reason if they wish to do so without any consequences. In case of withdrawal at any point during the hospital phase, treatment will be provided according to standard local clinical practice. The investigator can decide to discontinue the treatment to which a subject was randomized for urgent medical reasons.

As described in item 11a, patients initially randomized to group B can receive delayed secondary hematoma evacuation within the study protocol in case of neurological deterioration.

### Strategies to improve adherence to interventions {11c}

This is not applicable; as this is a surgical trial, there is no adherence issue after patients are randomized to either surgical intervention or initial conservative treatment with the possibility of delayed surgery in case of neurological deterioration. As described in items 11a and 11b, cross-over of patients from group B to group A is possible within the study protocol.

### Relevant concomitant care permitted or prohibited during the trial {11d}

The details of the treatments under investigation, including the specifics of the surgical procedure, the conservative-medical management protocol and concomitant care will be left up to the participating centers. Thus, this pragmatic trial takes existing variability into account and therefore allows for flexibility in delivery of the intervention and implementation of the results. Importantly, the general postoperative care on the ward or intensive care unit is not expected to differ substantially between Belgian and Dutch centers.

### Provisions for post-trial care {30}

The local site retains all responsibility, medical and otherwise, to provide the best care for their patients. The sponsor has a liability insurance (Centramed, [name], The Netherlands) which is in accordance with article 7 of the WMO. The Medical Ethical committee Leiden-The Hague has waived the obligation to take out an additional study subject insurance due to the absence of additional risk involved in participation.

### Outcomes {12}

#### Main study parameter/endpoint

The primary endpoint will be the Extended Glasgow Outcome Scale (GOS-E) at 1 year after injury [74]. The use of the GOS-E as a core global outcome measure is recommended by the interagency TBI Outcomes Workgroup and the International Mission for Prognosis and Analysis of Clinical Trials in TBI group (IMPACT Common Data Elements) [75]. The GOS-E [76], derived from its precursor the GOS [77], is globally the most commonly used TBI outcome measure. While the GOS grades disability on a 5-point scale and is determined largely by physical deficits, the GOS-E provides a higher sensitivity by defining disability on an 8-point scale and incorporating emotional and cognitive disturbances affecting disability. Especially in the elderly emotional and cognitive disturbances are described after undergoing complex cranial surgery, in particular in ASDH.

The GOS-E is designed as a structured interview and can also be applied through telephone [78] and e-mail [79]. This allows for long-term follow-up without a high burden for patients. Although several other primary outcome measures for TBI exist, the GOS(-E) remains the most widely implemented and best validated tool to assess outcome in TBI and permits comparison to much of the world literature on TBI outcome [80, 81]. In the (retired) elderly population, the GOS-E should be interpreted with reference to previous engagement (including reintegrating to former social and leisure activities instead of work per se) and the extent of any change, as in most people in this aged population there is absence of paid employment. Experienced research nurses will grade outcomes based on the GOS-E in each patient according to a standardized approach [76].

#### Secondary study parameters/endpoints

Secondary outcomes will be measured at 3, 6, 12, 24, 36, 48, and 60 months after randomization. Follow-up at 3, 6, and 12 months will be executed by live visits from research nurses from Leiden/Leuven. Other follow-up moments will be captured by postal or telephone, depending on the clinical state of the patient. As the GOS-E is a global outcome measure, cognitive, physical, social, and psychological disturbances may be insufficiently captured. Therefore, the widely adopted TBI-specific HRQOL questionnaire QOLIBRI [82–84] will also be used as an important secondary outcome. Furthermore, the EuroQol-5D-5L questionnaire will be used for the economic evaluation [85]. Cognitive functioning will be assessed by the Montreal Cognitive Assessment (MOCA) [86]. The four questionnaires are briefly described:

##### GOS-E

The Glasgow Outcome Scale (Extended) is (together with its precursor GOS) the most commonly used global outcome measure in TBI research.

##### QOLIBRI

The Quality of Life after Brain Injury is the first TBI disease-specific quality-of-life outcome tool that is cross-culturally developed and validated in large populations.

##### EQ-5D-5L

EuroQol-5D-5L is a 5-dimensional generic instrument assessing health-related quality of life and health status and generates an index of health for use in economic evaluations.

##### MOCA

The Montreal Cognitive Assessment is a widely used questionnaire assessing 8 domains of cognitive functioning. As the MOCA cannot be completed per telephone, it will only be performed during the live visits up to 12 months.

All secondary outcomes are listed below.
Functional outcome as expressed on the GOS-E besides the one year measurement (this includes mortality)Disease-specific quality of life as expressed on the QOLIBRIHealth-related quality of life as expressed on the EuroQol-5D-5LCognitive functioning as expressed on the MOCADirect and indirect costsDuration of hospital stayTime from event to surgeryDischarge locationsComplications (during hospital stay)Secondary surgery in both groups

#### Other study parameters

With regard to the second research question, the investigators aim to identify subgroups of patients who will benefit substantially from one of the proposed treatments. It should be noted that these subgroup analyses are explorative in nature as this trial has been powered based on the primary effect estimate.

The following subgroups will be investigated:
Elderly with accompanying cerebral contusions visible on first CT versus isolated ASDHs“Younger elderly” (aged 65–80 years) versus “older elderly” octogenarians (aged > 80 years)Elderly receiving specific oral anticoagulants or antiplatelets versus elderly not receiving such medication*Pre-trauma premorbid functionally independent of minimally dependent elderly (FIM score 4–7) versus functionally dependent elderly (FIM score 1–3) [69, 81]Elderly with severe comorbidities (ASA III-V) versus elderly with mild or no comorbidities (ASA I/II) [82, 83]Male versus femaleSurgical technique: basic hematoma removal by craniotomy versus add-on decompressionNo ICP monitoring versus ICP guided treatment taking into account cerebral perfusion pressureSubgroups stratified on (automatically generated) measurements of volumes and ratio of volumes of important intracranial traumatic findings on non-contrast CT in the acute phase

*A subdivision will be made between anticoagulants (e.g., coumarin derivatives/heparin/DOACs) and antiplatelets (e.g., aspirin/clopidogrel/dipyridamole).

### Participant timeline {13}

Eligible patients will be randomized in one of two groups (early surgery or initial conservative management) directly after the initial CT scan and informed or deferred consent. This will mostly occur after arrival at one of the participating neurosurgical centers but may also take place in affiliated hospitals prior to transfer depending on the local agreements and working methods. Several questionnaires will be obtained by visiting participants at discharge, 3 months, 6 months, and 1 year. Long-term follow-up will take place yearly via telephone, postal questionnaires, or digitally for up to 5 years. The design of the trial is depicted in Fig. 4 and Table 3 describes the follow-up evaluation.

**Fig. 4 Fig4:**
[figure not shown]
RESET-ASDH study design flowchart

**Table 3 Tab3:** Follow-up valuation

	Patient visit by research nurse				Telephone/postal			
Questionnaires	Discharge	3 months	6 months	1 year	2 years	3 years	4 years	5 years
Demographics	X							
GOS-E The Glasgow Outcome Scale (Extended) is (together with its precursor GOS) the most commonly used global outcome measure in TBI research	X	X	X	X^a^	X	X	X	X
QOLIBRI The Quality of Life after Brain Injury is the first TBI disease-specific quality-of-life outcome tool that is cross-culturally developed and validated in large populations		X	X	X	X	X	X	X
EQ-5D-5L EuroQol-5D-5L is a 5-dimensional generic instrument assessing health-related quality of life and health status and generates an index of health for use in economic evaluations		X	X	X	X	X	X	X
MOCA The Montreal Cognitive Assessment is a widely used questionnaire assessing 8 domains of cognitive functioning. As the MOCA cannot be completed per telephone, it will only be performed during the live visits up to 12 months		X	X	X				
Health economics Intramural care costs, patient costs and productivity loss of both patient and family will be determined through tailored patient questionnaires containing the relevant aspects of the iMCQ, iPCQ and iVIC questionnaires		X	X	X				X

^a^Primary outcome

### Sample size {14}

The sample size of 300 patients was based on an ordinal analysis method of the primary outcome. It was calculated analytically using PASS software version 11 and achieves a 90% power to detect a change in the log odds ratio of 0.69 with a 0.05 (two-sided) significance level, allowing for a loss of follow-up of 8%. Calculations were based on the expected percentage distribution of conservatively treated patients over the GOS-E categories 1–8 (15, 10, 10, 10, 10, 10, 15, 20) with category 1 and 2 combined and an estimated (adjusted) proportional odds ratio of 2.0 representing the targeted treatment effect that is considered clinically relevant in the management of elderly with a traumatic ASDH. Table 4 shows the corresponding distribution of patients over the GOS-E outcome categories. The rationale for combining GOS-E categories 1 and 2 in the statistical analysis is the opinion of the researchers that a potentially large shift of patients from category 1 (death) to category 2 (vegetative state) should not result in a positive trial as this cannot be considered a beneficial or positive effect of surgery.

**Table 4 Tab4:** Estimated shift over GOS-E outcome categories

GOS-E	1&2	3	4	5	6	7	8
Patient’s condition	Dead and vegetative state	Lower severe disability	Upper severe disability	Lower moderate disability	Upper moderate disability	Lower good recovery	Upper good recovery
Initial conservative treatment (%)	25	10	10	10	10	15	20
Early surgery (%)	14	7	8	9	10	19	33

### Recruitment {15}

Ultimately, 300 patients will be included in the study. Yearly, a total of approximately 460 elderly patients are expected to present with a traumatic ASDH in all participating research centers combined. ASDH patients present to one of the participating hospitals during the inclusion period. From previous experience with CENTER-TBI and Net-Qure, it is estimated that approximately 25% of all consecutive ASDH patients in the centers will meet 1 or more exclusion criteria and 10% will refuse participation (with probably little higher refusal rates in large urban hospitals based on previous big-city experiences of the investigators). Based on the previously mentioned STITCH trial and clinical experience of the investigators, it is estimated that “clinical equipoise” will be present in approximately 85% of cases. Thus, the investigators estimate that approximately 50% of screened patients will actually get randomized. To achieve an inclusion of 300 patients, a 2-year recruitment period is estimated. A 32% margin for unforeseen issues has been taken into account in the calculation of the inclusion period. Importantly, neurosurgeons in all participating centers will be extensively tutored on location to become more familiar with the concept of “clinical equipoise” during planned visits by the PI and research team before start of the trial in order to optimize patient recruitment.

## Assignment of interventions: allocation

### Sequence generation {16a}

Randomization will take place with a 1:1 allocation ratio via a web-based randomization program by the treating clinician or including researcher and will be stratified by center and blocked with alternating block sizes of 2, 4, and 6. The randomization process will be recorded by the web-based randomization system. A 24-h randomization service will be backed by 24-h availability of the research team, who will also be able to advise on patient eligibility. In case of web-related problems, the treating clinician or including researcher will undertake randomization instead by manually opening a prefabricated sealed envelope containing a category.

### Concealment mechanism {16b}

A web-based randomization program will be used. In case of web-related problems, the treating clinician or including researcher will undertake randomization instead by manually opening a prefabricated sealed envelope containing a category. See also item 16a.

### Implementation {16c}

The treating clinician or including researcher will perform randomization via a web-based randomization program. See also item 16a.

## Assignment of interventions: Blinding

### Who will be blinded {17a}

It is not possible to blind either patients or treating neurosurgeons to whether or not the patient receives surgical hematoma evacuation. For organizational and ethical purposes, it is also not possible to blind the outcome evaluators, being the research nurses. The PhD students analyzing the data will however be blinded for the allocated treatment arm by means of a database that does not reveal the study group assignment.

### Procedure for unblinding if needed {17b}

This is not applicable; no unblinding will be necessary for the PhD students analyzing the data.

## Data collection and management

### Plans for assessment and collection of outcomes {18a}

#### Handling and storage of data and documents

After randomization, clinical care and medical documentation will take place according to local site protocol. Dedicated research nurses from Leiden/Leuven will collect all relevant data, such as pre-hospital, clinical, and imaging data. Data collection is done in standardized electronic databases, based on the “common data elements” for TBI and web-based data collection protocol [87, 88].

### Plans to promote participant retention and complete follow-up {18b}

Experienced research nurses for Leiden/Leuven will collect all relevant data, such as pre-hospital, clinical, and imaging data. In case of no response, attempts will be made to contact patients via their legal representative and/or general practitioner. If follow-up data from a patient is missing, values will be imputed based on other available follow-up data from that patient. Only patients without any follow-up data (including the 3-month assessment) will be considered “lost to follow-up”. This includes patients whose (deferred) consent is withdrawn before the 3-month follow-up assessment. Patients who have died soon after randomization will be included in the analysis as “death” is one of the outcome categories in the primary outcome measurement (GOS-E). Patients who were wrongfully included due to mistakes in the evaluation of objective entry criteria such as age (eligibility violations) will be considered “non-eligible” in the second instance. The amount of patients “lost to follow-up” or “non-eligible” in the second instance is estimated to be a very small proportion of all study patients (< 5%).

### Data management {19}

All relevant clinical data will be entered into electronic Case Report Forms (eCRFs). Data storage and backup will be managed by the CASTOR data management platform.

#### Integration with analytic platforms

The RESET-ASDH dataset will be registered on the DANS/easy archiving and networking service. The Dublin Core generic metadata scheme will be used for description of the data collection. Together with the CASTOR systems, the International Neuroinformatics Coordinating Facility (INCF) will ensure that data standards are established for the data model, e.g., conformity of field formats, field codes, and names to ensure consistency across all datasets. INCF will also be responsible for importing cleaned datasets to other analytic platforms as determined by the coordinating researchers.

### Confidentiality {27}

Data will be handled confidentially and coded in compliance with the European Union General Data Protection Regulation (GDPR) (In Dutch and Flemish: Algemene Verordening Gegevensbescherming). The CASTOR encryption module will be used to encrypt information capable of identifying individuals. The encryption code will only be available to selected members of the research team as well as independent data monitors and the Health and Youth Care Inspectorate (IGJ). All analyses will be performed on de-identified pseudonymized coded data, for which explicit permission is given in the patient informed consent form. A subject identification code list will be used to link the data to the subject when needed for data collection. Once assigned, the number will not be reused if the patient is excluded. After completion of the study, the key file will be archived in the hospital’s study documentation on a protected location on the network hard drive for 15 years in accordance with article 17 of the EU GCP directive. Patients or their legal representatives can withdraw their permission for data collection and storage at any time without consequences for the medical treatment. Any planned follow-up study visits will subsequently be canceled. Data that has already been collected before withdrawal of permission will be used for the analyses, unless specifically declined. A Data Protection Officer will be installed for the study to answer potential questions regarding processing of personal data and the involved legal aspects. For general information about data processing, either the Leiden University Medical Center (LUMC) or the Dutch Data Protection Authority can also be contacted.

### Plans for collection, laboratory evaluation, and storage of biological specimens for genetic or molecular analysis in this trial/future use {33}

This is not applicable; no biological specimens are collected.

## Statistical methods

### Statistical methods for primary and secondary outcomes {20a}

The primary outcome in this study will be the GOS-E at 1 year. Traditionally, such outcome scales are analyzed by dichotomizing the ordinal scale into a binary scale by defining outcome as “unfavorable” or “favorable” and calculating an odds ratio. However, many patients will not have a realistic opportunity to cross the threshold between “unfavorable” and “favorable” and will therefore not contribute data to the analysis. The crude odds ratio is thus not a meaningful effect measure for a large number of patients and discards much relevant information, reducing both the clinical relevance of the results and the statistical efficiency of the analysis. Therefore, the researchers consider it more appropriate to quantify effects across the full range of the GOS-E. In line with the IMPACT recommendations (NIH-funded International Mission for Prognosis and Analysis of Clinical Trials in TBI project), the investigators plan to analyze the primary outcome by using a proportional odds regression with covariate adjustment for age, GCS, and pupillary reactivity to adjust for baseline imbalances and to optimize statistical efficiency. Ordinal methods have been shown to increase statistical power substantially compared to traditional dichotomous analyses, equivalent to allowing a reduction of over 40% in the sample size without loss of statistical power. The primary effect estimate will be the adjusted proportional odds ratio with 95% confidence interval for the shift in the direction of a better outcome on the GOS-E. Ordinal logistic regression analysis is similar to logistic regression analysis, except for the fact that it estimates multiple odds ratios instead of one. The number of odds ratios is equivalent to the number of categories minus one. The final estimated effect size is a pooled estimate of the common odds ratio. The ordinal regression model assumes that the odds ratio for each potential cut of the GOS-E is constant no matter which cut-off point is taken (proportional odds assumption). Although the common odds ratio is formally only valid if the proportional odds assumption is met, the common odds ratio can be interpreted as a summary measure of treatment effect, even if the odds ratios differ by cut-off [89, 90].

In this study, the common odds ratio can be interpreted as the average shift over the GOS-E scale at 1 year caused by early neurosurgical intervention compared to non-operative management [90].

The investigators hold the opinion that a potential large shift of patients from GOS-E category 1 (death) to 2 (vegetative state) should not be considered a beneficial effect of surgery and should not result in a positive trial. Therefore, these categories will be combined in the final statistical analysis. As this trial is pragmatic, results will be analyzed according to an intention-to-treat protocol. Predefined subgroups for exploratory analyses are described below. The secondary outcomes will be analyzed using the appropriate tests. A *p*-value of less than 0.05 will be used to indicate statistical significance. For all analyses, commercially available statistical software like SPSS or R will be used.

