The most frequently encountered pathological entity in TBI patients is an acute intracranial hematoma. Specifically, an acute subdural hematoma (ASDH) is the most common injury in elderly TBI patients and is often accompanied by a cerebral contusion [8, 9]. The enlarged subdural space of the progressively atrophic aging brain is associated with increased tension on bridging veins, making them more susceptible to shearing damage. Furthermore, the widespread use of anticoagulants and antiplatelet drugs among elderly increases the risk for ASDH development, even after low to moderate energetic head trauma [10]. Traditionally, older age has been closely associated to poor outcome after TBI [11, 12], partly because of comorbid illnesses negatively influencing outcome [12]. In reports from the 1980s and 1990s, mortality rates for patients aged ≥65 with an ASDH approached 90% [13, 14]. Hence, elderly patients have long been treated less “aggressively” compared to the younger patient population because of the presumed poor prognosis [10]. Over time, with faster transfers directly from accident to level I trauma hospitals, improved diagnostic tools and acute medical and intensive care, mortality rates in elderly patients with ASDH have declined from 90 to between 30 and 60% [15]. Along with this, neurologists’, trauma- and neurosurgeons’ traditional reserved attitude towards elderly patients has gradually shifted towards a more “aggressive” surgical approach [16, 17]. Despite this trend towards a more intensive treatment approach in the elderly sustaining TBI, the question whether to surgically or conservatively manage elderly patients with an ASDH remains a matter of huge controversy [18]. Surgical evacuation of the hematoma can be lifesaving, but is not necessarily restorative and may leave patients in a questionable quality of life, with huge costs to family and society [19–22]. Conversely, non-operative management may prompt favorable outcome in some patients, but can also result in—potentially preventable—death and disability [23, 24]. At present, it is not possible to accurately predict whether a specific patient will benefit from a certain treatment in terms of survival, functional recovery, and quality of life. This heterogeneity can be caused by many factors, including gender, anticoagulant/antiplatelet use, premorbid functioning, comorbidities, age, and the presence or absence of intracerebral contusions accompanying the ASDH. Current Brain Trauma Foundation (BTF) guidelines for the surgical management of TBI recommend the surgical removal of an ASDH measuring > 10 mm or when it causes a midline shift > 5 mm, regardless of a patient’s neurological state (Glasgow Coma Scale (GCS) score) [25]. These guidelines, released in 2006, are based on low-grade (class C) evidence from the 1990s and thus provide only limited guidance in modern clinical practice, allowing for subjective care and practice variation [23–26]. Indeed, great variation in BTF guideline adherence has been reported, ranging from 18 to 100% between studies [27, 28]. Moreover, major practice variation exists in Belgium and The Netherlands with regard to the management of traumatic ASDHs between centers, and even between neurosurgeons in the same center [29–31]. This variability in TBI management goes alongside unexplained variability in outcome and large between-center differences unrelated to case-mix [32–34].

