#### Exclusion criteria

A potential subject who meets any of the following criteria will be excluded from participation in this study:
Additional epidural hematoma (EDH) or infratentorial (e.g., cerebellar) intracerebral hemorrhage (ICH)Major traumatic abdominal or thoracic injury (each separately defined as an Abbreviated Injury Scale (AIS) score ≥ 4) [66, 67] or a “moribund” state at presentation (e.g., bilaterally absent pupillary responses)Known terminal condition resulting in a life expectancy of less than 1 yearSevere and progressive dementia or cerebral infarction necessitating daily care in a nursery home in the pre-trauma period

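### Adding pre-injury FIM and ASA class to the primary model's covariates is a cheap efficiency gain, probably small; the stated N and power do not depend on it

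*Protocol article*

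**What the plan says.** Statistical methods {20a} fixes the primary analysis as "proportional odds regression with covariate adjustment for age, GCS, and pupillary reactivity to adjust for baseline imbalances and to optimize statistical efficiency". The basis given is the general TBI guidance: "In line with the IMPACT recommendations (NIH-funded International Mission for Prognosis and Analysis of Clinical Trials in TBI project".

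Pre-trauma function and comorbidity appear elsewhere:

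- Other study parameters, under Outcomes {12}, lists exploratory subgroups by FIM ("Pre-trauma premorbid functionally independent of minimally dependent elderly", scores 4–7, against scores 1–3) and by ASA class (I/II against III–V).
- Background and rationale {6a} attributes part of the poor prognosis at older age to comorbid disease. Discussing which patients benefit from which treatment, it then says: "This heterogeneity can be caused by many factors, including gender, anticoagulant/antiplatelet use, premorbid functioning, comorbidities, age".

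Sample size {14} states: "The sample size of 300 patients was based on an ordinal analysis method of the primary outcome". It says that this number "achieves a 90% power to detect a change in the log odds ratio of 0.69", for "an estimated (adjusted) proportional odds ratio of 2.0", at two-sided 0.05 and with 8% loss to follow-up. Sequence generation {16a} stratifies by centre only.

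**The concern.** The covariates are chosen partly for efficiency, so the set can be judged against that aim. In a proportional-odds model, leaving out a variable that predicts the outcome pulls the treatment odds ratio towards 1 and costs some power. It also leaves chance imbalance in that variable uncorrected, and here randomisation does not balance pre-injury dependence or comorbidity.

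The three chosen covariates come from general TBI practice, and the entry criteria narrow their range to some extent. Age starts at 65. A GCS below 9 is admitted only with a small haematoma and little midline shift. The moribund state that is excluded is illustrated by "e.g., bilaterally absent pupillary responses". FIM and ASA must be recorded anyway for the subgroups. At stake is some precision in the single primary test.

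**Working it through.** **1. The plan's own figure.** Inputs from Sample size {14} and Table 4: control distribution 25, 10, 10, 10, 10, 15, 20% (GOS-E 1 and 2 merged), OR 2.0, two-sided 0.05, power 90%, 1:1 allocation.

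- Shifting the control distribution by OR 2.0 gives 14.3, 6.9, 7.8, 8.9, 10.2, 18.5, 33.3%, which agrees with Table 4 to rounding.
- Whitehead's formula is N = 12(z₀.₉₇₅ + z₀.₉₀)² / [(ln 2)²(1 − Σp̄³)], with p̄ the mean of the two arms. Here Σp̄³ ≈ 0.0344, so N = 12 × 10.507 / (0.4805 × 0.9656) ≈ 272.
- With 8% loss, 272/0.92 ≈ 296, against the stated 300.
- With 300 × 0.92 = 276 evaluable patients, power is 90.4%.

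The stated N and power are therefore reproduced with no contribution from FIM or ASA.

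**2. Effect of adding FIM and ASA, if OR 2.0 is the effect given all covariates.** The documents give no prevalence or prognostic strength for either variable, so these are assumptions. Trials of 276 patients were simulated with the Table 4 control distribution. Age, GCS and pupils were represented by one score with log OR 0.9 per SD. FIM and ASA were binary, correlated 0 or 0.3 with that score. Each setting had 4,000 runs with a Wald test at 0.05 (Monte Carlo error about 0.5 points). Ranges cover the two correlations; the last two rows use correlation 0.3 only.

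| Assumed FIM / ASA odds ratios | FIM-dependent / ASA III+ | Power, protocol model | Power, FIM and ASA added | Gain (points) | Mean OR, protocol model |
|---|---|---|---|---|---|
| 1 / 1 | 10% / 40% | 88.9–89.4 | 89.0–89.2 | −0.2 to 0.1 | 2.01–2.02 |
| 1.5 / 1.3 | 10% / 40% | 88.1–89.2 | 88.6–89.5 | 0.3–0.5 | 2.00 |
| 2 / 1.5 | 10% / 40% | 88.0–88.4 | 88.9–89.1 | 0.7–0.9 | 1.99 |
| 2 / 2 | 10% / 40% | 86.8–88.0 | 88.2–89.8 | 1.4–1.8 | 1.97–1.98 |
| 3 / 2 | 10% / 40% | 85.6–85.8 | 88.4–88.6 | 2.6–3.0 | 1.94–1.96 |
| 4 / 3 | 10% / 40% | 82.5–83.2 | 88.1–88.3 | 5.1–5.6 | 1.89–1.90 |
| 3 / 2 | 25% / 50% | 84.7 | 88.2 | 3.5 | 1.93 |
| 4 / 3 | 25% / 50% | 79.6 | 87.5 | 7.9 | 1.85 |

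**3. If OR 2.0 belongs to the age/GCS/pupils model.** This is the more natural reading, since {20a} makes that model's adjusted OR the primary estimate. The protocol model then keeps about 89% power. Adding a FIM/ASA score with log OR 0.3, 0.5 or 0.7 per SD gives 89.8%, 91.4% or 93.3%.

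**4. What a large gain would require.** Take a single binary dependence indicator with assumed prevalence 20% and latent correlation ρ = g/√(g² + π²/3), where g is the coefficient per SD. The implied odds ratio is exp(g/√(0.2 × 0.8)):

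- ρ = 0.3: g = 0.570, OR ≈ 4.2
- ρ = 0.4: g = 0.792, OR ≈ 7.2
- ρ = 0.5: g = 1.047, OR ≈ 13.7

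Simulated power without and with that indicator was 85% and 89%, 82% and 88%, and 78% and 88%. A gain above 5 points from one such indicator thus needs a residual odds ratio well above 4.

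**5. Type I error.** With a true OR of 1, adding a continuous FIM/ASA score left the error rate at about 5%.

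**The case against.** The strongest reply is that nothing here is wrong. The covariate set is prespecified with a stated basis, and the sample size claims no help from FIM or ASA. That stands. A reader might infer that the omission breaks the 90% power claim. The documents do not support this: the claim reproduces without these variables, and the shortfalls in step 2 arise only if OR 2.0 is taken as conditional on FIM and ASA as well.

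A reader might also infer that the protocol names both variables as drivers of outcome. It does so for comorbidity. Premorbid functioning is listed for heterogeneity in who benefits, which is a different matter.

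The residual prognostic value may be modest. The exclusions remove nursing-home dependence from severe dementia or infarction, and life expectancy under a year. Main study parameter/endpoint {12} has the GOS-E read against the patient's earlier level of activity, which may absorb part of the effect of prior function. Age already carries some of it. These points limit the gain but do not remove it: FIM 1–3 and ASA III–V remain planned subgroups, and death is an outcome category that comorbidity can still influence.

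Finally, it would be too strong to say that the change costs nothing. The consent section {26a} says surrogates are mostly unavailable acutely, so pre-trauma FIM may be missing or recalled later. Data are gathered after randomisation ({18a}) by research nurses who are not blinded ({17a}). A recalled baseline value could be coloured by arm or outcome. This stands, and the fix has to deal with it.

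**Conclusion.** The point holds as an optional, low-cost efficiency improvement. The primary model leaves out two baseline variables that the trial needs anyway, one of which the protocol itself ties to outcome. The likely gain is about 0 to 3 points of power under weak to moderate residual effects, and about 5 to 8 points only if FIM and ASA are both strong beyond age, GCS and pupils (odds ratios of about 4 and 3).

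For scale, moving from 86% to 88.5% power corresponds to (1.960 + 1.200)² / (1.960 + 1.080)² ≈ 1.08, or roughly 22 more evaluable patients on 276.

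All these figures rest on assumed prevalences and prognostic strengths, because the documents give none. Only the protocol article was available; an analysis plan may already extend the set.

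**What to change.** In {20a} or the analysis plan, before any outcome is seen by arm:

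- Extend the primary covariates to age, GCS, pupillary reactivity, pre-injury FIM and pre-injury ASA class, with FIM and ASA on their recorded scales rather than the subgroup cuts.
- Take both from pre-injury information, recorded or settled without knowledge of arm or outcome.
- Impute missing baseline values from other baseline data, without using arm.
- Report the model with age, GCS and pupils only as a sensitivity analysis.

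The cost is a sentence or two of text, a few extra model parameters, and some care over when and by whom FIM and ASA are settled. No new visits or variables are needed, since the subgroups already require both. Missing or proxy-recalled FIM values will reduce the gain.
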